#### Quantitative data collection and measures

We will quantitatively evaluate implementation outcomes using two proxy measures for implementation: uptake and usage. Uptake will be measured at the end-user level as a binary indicator of whether the end-user logged in to the Gabby System at least once. Usage will be measured also at the end-user level as the number of logins to the Gabby System and the number of minutes spent using Gabby. Usage and uptake will be collected at 3 and 5.5 months.

In addition, following the organizational readiness interview, community partners will be asked to complete a corresponding scale based 33-question Qualtrics XM® survey that will be used to assess organizational readiness while examining affirming, contradictory or conflicting findings elicited during the organizational readiness interview. Participating community partner staff will receive the survey via email from the academic research staff and will be allotted 72 h from the time that they finish their organizational readiness interview to complete the quantitative survey. The purpose of the Likert scale based Qualtrics XM® survey is to complement the organizational readiness interview and serve as a validation of barriers and facilitators identified at the site. Responses along the 5-point Likert scale will consist of Strongly Disagree (1), Disagree (2), Neutral (3), Agree (4), Strongly Agree (5). This approach will allow for rapid data collection and timely turnaround of analysis and stratification of results by type of staff for actionable steps within a relatively short timeframe at every community site during this critical pre-launch phase.

We will evaluate the clinical effectiveness of the intervention through reports produced by the Gabby System server. For each client/patient we will track: (1) baseline stage of change data obtained for each risk identified during the client/patient’s interaction with the Gabby System; (2) follow-up stage of change data to identify the progression (or regression) in the changes associated with each health risk; (3) risk resolution based on the percentage of subjects reaching the action and maintenance stage for each risk at 3 months and 5 ½ months during the implementation period.

### Analysis

#### Qualitative analysis

Two members of the academic research team will jointly code initial interview transcripts as they are completed using evaluation and framework coding methods [41, 42]. Data analysis will be guided by an a priori coding dictionary based on the existing CFIR codebook, definitions, and coding criteria [43]. Data not aligned with the CFIR codebook will be coded using novel codes following concept coding methods [41]. The coding dictionary will be revised iteratively, and coding discrepancies will be resolved by reviewing the coding dictionary and the relevant section of the interview transcript. When revisions to the coding dictionary are finalized and no new codes emerge, both team members will code the remaining interview transcripts independently. Research team members will engage in reflective analytic practices, and codes most frequently used and appearing in at least two interview transcripts will be selected for secondary analysis. A summary of preliminary findings will be presented to the research team during regular team meetings and shared with site staff members during the facilitators, barriers and logistics discussion prior to the Gabby System training (See Fig. 2). Transcript data will be managed using Dedoose version 8.2.14, an online platform that allows for multiple research team members to simultaneously and collaboratively code and analyze transcript data [44].

#### Quantitative analysis

Implementation outcomes (acceptability, appropriateness and feasibility) will be quantitatively assessed based on uptake (whether each end-user logged in to the Gabby System at least once) and usage (number of logins, and number of minutes spent using Gabby, per end-user), at 3 and 5.5 months. By definition, uptake and usage will not have baseline values, but we will descriptively assess uptake and usage from 3 to 5.5 months. We will also use OLS regression with site fixed effects to assess the relationship between uptake or usage and relevant secondary covariates.

Relevant secondary covariates will be assessed using a 33-question Likert scale-based survey. Scale-based responses allow for an interpretable organizational readiness score that can be compared across CFIR domains, constructs, staff levels, and sites. Composite scores will be constructed by calculating the mean score across all survey questions and aggregated into a broader organizational readiness score. Descriptive analysis will be used to assess the relationship between composite scores and site level characteristics. Independent t-tests will also be used to assess the relationship between domain composite scores and site characteristics; for any subgroup analyses or to control for additional covariates, OLS regression will be used. In addition, domain scores and aggregate organizational readiness scores will be assessed at the individual staff level in two ways. First, OLS regression with site fixed effects will be used to assess the relationship between staff-level domain and organizational readiness scores and staff characteristics. Second, a multi-level random-effects model will also be used to assess relationships between staff-level domains and organizational readiness scores and the same staff characteristics. Thematic codes derived from qualitative interview data described above will be used to support and provide context for scale-based responses. This mixed-methods approach to assessing organizational readiness allows for a broader understanding between the relationship of Likert scale responses and inclusive narrative from stakeholder interviews.

To assess the effectiveness of Gabby, we will measure the rate of risk behaviors per subject at action and maintenance. Stage of change data will be collected at the initial assessment, at 3 months, and again at 5.5 months, and then compared across the three data collection points for triggered risks. We anticipate that subjects receiving an effective Gabby intervention should see a greater number of risk behaviors, from baseline to 3 and then 5.5 months, that have reached the action or maintenance stage of change. We will also assess the rate of risk behaviors per subject progressing forward on the stage of change scale. We will test for the effectiveness of Gabby by using a Poisson model to regress our stage of change rate outcomes on data collection time point, with site fixed effects. In addition, for each risk, a logistic regression model will be used to regress a binary measure of whether that risk had either remained at the action or maintenance stage or progressed forward, data collection time point, with site fixed effects.

Finally, we will run analyses to determine whether Gabby was differentially effective conditional on baseline stage of change. This will be done by restricting the data only to risks that were reported at “pre-contemplation” at baseline; then by calculating the rate that remained at “action” or “maintenance” or progressed forward, and finally by regressing that rate on the period of data collection using a Poisson model with site fixed effects. This procedure will be repeated by restricting the data to risks reported at “contemplation” at baseline, and again by restricting risks reported at “preparation” and then “action” stages of change. All statistical tests will be run at alpha level a = 0.05 and performed using the R programming language, version 3.4.3 [45].

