##### Technical assistance

For one month following the launch, the academic partner will provide technical assistance in the form of weekly calls with participating community partners. A semi-structured guide (Additional file 4) will be used to facilitate technical assistance calls and to capture a realistic sense of the progress of recruitment and implementation efforts. The calls will gauge any gaps in the pre-implementation process, resolve issues and identify resources to improve recruitment and engagement of staff and end-users. Technical assistance following the one-month requirement will occur as requested by the community partner. Community partners will also complete monthly implementation logs (Additional file 5) that capture reach (the proportion of Black and African American women willing to participate in the intervention), enrollment (the proportion of women who initiate engagement with Gabby), follow-up and referrals on flagged PCC-related risk factors (e.g. genetic health history, social and emotional well-being, healthcare access and affordability), and any technical issues that end-users and staff encountered. The primary purpose of the implementation log is to provide a quick snapshot of monthly implementation activities that inform reach, enrollment and the nature of interactions that frontline staff have with end-users about Gabby and/or PHHC topics discussed on a monthly basis.

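### The planned OLS of end-user uptake or usage on staff-survey readiness, with site fixed effects, cannot estimate the readiness coefficient, because the score is constant within a site.

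*Protocol article*

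**What the plan says.** The Quantitative analysis section of the protocol article first says that uptake and usage will be described at 3 and 5.5 months. It then adds a regression: "We will also use OLS regression with site fixed effects to assess the relationship between uptake or usage and relevant secondary covariates". The following paragraph opens by saying where those covariates come from: "Relevant secondary covariates will be assessed using a 33-question Likert scale-based survey".

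The section on quantitative data collection and measures fixes the level of each variable.

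- **Outcome.** "Uptake will be measured at the end-user level as a binary indicator of whether the end-user logged in to the Gabby System at least once". The same level applies to usage (logins and minutes).
- **Covariate.** "Participating community partner staff will receive the survey via email from the academic research staff". The stated advantage of the survey is a quick turnaround "within a relatively short timeframe at every community site during this critical pre-launch phase", so it is a single pre-launch measurement.
- **Scoring.** The Quantitative analysis section states: "Composite scores will be constructed by calculating the mean score across all survey questions and aggregated into a broader organizational readiness score".

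The article names no end-user characteristic as a covariate for this model. It also does not say that an end-user will be given the score of the staff member who introduced her to the system.

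**The concern.** The outcome varies between women within a site. The covariate, as described, varies only between sites. Site fixed effects remove all between-site variation, which is the only variation that readiness has.

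This regression is the only planned quantitative link between how ready a site was and how much its clients used the system. If it is run as written, one outcome is a missing coefficient. The worse outcome is a coefficient that looks normal and means nothing, printed with a standard error based on the number of women rather than the number of sites. That second result could reach a report or the implementation toolkit unnoticed.

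**Working it through.** The plan gives no figure to reproduce here. The check is whether the stated model identifies the stated coefficient.

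**Inputs**

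- Sites: 12 (Sample size and power calculation).
- End-users per site: 20 (Sample size and power calculation) or 25 to 50 (Abstract), so N = 240, 300 or 600.
- Staff interviewed per site before launch: 5 to 10 (Qualitative data collection and measures). They receive the survey after the interview, and their answers are averaged to the site.
- Readiness: one overall score per site, or one for each of the five framework domains per site.

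**Algebra.** For end-user i in site s the model is

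y_is = α_s + β·R_s + e_is,

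where α_s is the site effect and R_s the site's readiness score. For any constant c, replacing β by β + c and each α_s by α_s − c·R_s leaves every fitted value unchanged. The data therefore cannot distinguish one β from another. Equivalently, the fixed-effects estimator divides by the within-site sum of squares of readiness, Σ(R_is − R̄_s)², which is zero because every woman in a site carries the same R_s.

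**Rank of the design matrix**

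| Design | Columns | Rank | Readiness estimable? |
|---|---|---|---|
| 12 site indicators + overall score; N = 240, 300 or 600 | 12 + 1 = 13 | 12 | No |
| 12 site indicators + overall score + five domain scores | 12 + 6 = 18 | 12 | No |
| Both time points stacked: 12 site indicators + time + score | 12 + 1 + 1 = 14 | 13 | No |
| 12 site indicators + a covariate that varies between end-users | 13 | 13 | Yes, for that covariate |
| Intercept + score, no site fixed effects | 2 | 2 | Yes |

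The computed within-site sum of squares of the score was about 1e-29 to 1e-28, which is zero apart from rounding. The rank is the same at 20, 25 and 50 end-users per site, so more recruitment does not help.

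**What software would do.** The article names R. If site is entered first, the readiness coefficient is returned as missing. If readiness is entered first, the last site indicator is dropped. Only the reference site and the dropped site then lack an indicator of their own, and the printed slope is

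β̂ = (ȳ_dropped − ȳ_reference) / (R_dropped − R_reference).

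This is a comparison of two sites out of 12. Relabelling the sites changes it, and its standard error ignores site-to-site variation.

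**Information actually available.** With one score and 12 site values the residual df are 12 − 2 = 10. The two-sided 5% critical t is 2.228, so

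|r| = 2.228 / √(2.228² + 10) = 2.228 / 3.868 = 0.576.

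Readiness would have to account for about a third of the variance of the site means (0.576² = 0.33) to reach p<0.05. If all five domain scores entered together, 12 − 6 = 6 df would remain.

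**The case against.** **The covariate list may be incomplete.** The article is condensed, it does not list covariates in full, and it is silent on how scores attach to end-users. Scores do exist for individual staff, and trained staff introduce the system to clients. If each woman carried the score of the person who introduced her, or if end-user characteristics were meant, the model could be estimated. This stands as a condition on the finding. It does not remove it, because the only source the text gives for these covariates is the staff survey, and it describes no such link. If either was intended, it has to be written down.

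**The regression is an add-on.** The sample size section says that usage and uptake are analysed descriptively, and no listed aim or objective is to estimate an association between readiness and uptake. This stands, and it limits how serious the point is.

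**Stronger readings that a reader might infer**

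- *Uptake has no variance.* The Technical assistance section defines "enrollment (the proportion of women who initiate engagement with Gabby", and uptake means at least one login. Someone could conclude that every enrolled woman has uptake by definition. But that definition belongs to the monthly site logs. Elsewhere end-users are the clients or patients to whom staff introduce the system, and not all of them need log in. The wording is loose, but it does not establish zero variance.
- *Uptake should be redefined from those logs.* The logs are monthly site snapshots. They do not supply the end-user indicator that the plan defines, and the change would alter a measure in a study already in the field.
- *OLS is the wrong model for these outcomes.* Linear regression of a binary outcome estimates risk differences. For counts or minutes it estimates mean differences, and robust standard errors can deal with unequal variance. Nothing in the article shows a material error from this choice.

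**Conclusion.** The concern holds for the model as stated. A site-constant readiness score and site fixed effects cannot appear together in a regression of end-user uptake or usage. The design is one rank short (12 of 13), and no sample size corrects that. This is a conflict between a stated model and its stated covariates, not a detail left for a later analysis plan.

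It rests on three assumptions: the covariates in this regression are the survey scores, the survey is taken once before launch, and scores are not linked to end-users through individual staff. The figure of 10 df further assumes 12 sites and one score. With J sites the rank is J of J + 1, and J − 2 df remain.

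The reach is limited to a secondary regression under aim 1. A reader might infer that aim 1 as a whole fails, but the documents do not support that: the descriptive uptake and usage results and the interviews do not depend on this model. The staff-level readiness models are also sound, because there the score is the outcome and staff characteristics vary within site (rank 13 of 13 in a simulated staff data set). The effectiveness analysis does not use readiness. The wording should be corrected before the regression is run, but the point does not threaten the main results.

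**What to change.** In the Quantitative analysis section, separate the covariates by level.

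- **Site-level covariates, including overall and domain readiness.** Drop the site fixed effects. Either fit the end-user model with a site random intercept, or regress the 12 site means of uptake and usage on readiness. Base inference on between-site degrees of freedom, and report that the information is 12 sites (about 10 residual df for one score) whatever the number of women enrolled.
- **Covariates that vary among end-users within a site.** Keep the site fixed effects and name the covariates.
- **If staff scores are to be linked to end-users,** state the linkage and how it will be recorded.

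The article already specifies a multi-level random-effects model for the staff-level scores, so the approach is not new to the plan. The first two changes need only a change of wording and no new data. The costs are statistical: intervals will be wide with 12 sites, and without site fixed effects the readiness slope is open to confounding by other site characteristics, such as Healthy Start program versus Community Health Center. The result should be presented as exploratory.

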### Sample size and power calculation

To assess implementation based on usage and uptake, we will treat the sample size calculated for effectiveness as a convenience sample. Because usage and uptake are being analyzed descriptively with no baseline data and no over-time comparison, it is not appropriate to calculate power for these outcomes.

To assess effectiveness based on per-end-user stage of change outcomes, our target sample size calculation is based on 12 available sites. Based on our previous RCT of 528 African American/Black women recruited nationally, [19] we expect to see an approximately 7.3% difference in the rate of risks behaviors achieving action or maintenance from 0 to 5.5 months, with a common error variance of approximately 28.7%. With paired two-sided tests, at a power of 0.80 and a significance level of 0.05, we would require at least 125 subjects to detect an effect of at least this magnitude. Because end-users are nested within sites, we also must account for within-site clustering. Based on published intra-class correlation coefficient (ICC) data from 61 clinical practices in 8 practice based research networks on risks such as smoking, diet, and exercise, we anticipate an ICC of 0.012 and a design effect of 1.3 [33]. Based on this design effect, we require at least 160 end-users, or 13 end-users per site. If we anticipate only about 2/3 of end-users to provide outcome data (consistent with our previous study), then we must enroll approximately 240 users, or 20 end-users per site, to detect a change in our outcome from 0 to 5.5 months.

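### The Poisson model for the action/maintenance rate is unpaired although the study is sized on paired tests, so with one third expected to be lost, the time effect can mix selective return with behaviour change

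*Protocol article*

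**What the plan says.** The Quantitative analysis section of the protocol article sets the main effectiveness outcome: "we will measure the rate of risk behaviors per subject at action and maintenance". The schedule is "Stage of change data will be collected at the initial assessment, at 3 months, and again at 5.5 months", and the values are "and then compared across the three data collection points for triggered risks". The test is carried out by "using a Poisson model to regress our stage of change rate outcomes on data collection time point, with site fixed effects". Time point and site are the only terms named. A second rate outcome is "We will also assess the rate of risk behaviors per subject progressing forward on the stage of change scale", and a per-risk logistic model uses whether the risk stayed at action or maintenance or moved forward.

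The Sample size and power calculation section plans the same contrast differently. It expects an "approximately 7.3% difference in the rate of risks behaviors achieving action or maintenance from 0 to 5.5 months" and uses paired two-sided tests at power 0.80 and significance level 0.05. That gives 125 women, raised to 160 for clustering. On loss it says: "If we anticipate only about 2/3 of end-users to provide outcome data (consistent with our previous study", and "then we must enroll approximately 240 users, or 20 end-users per site".

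**The concern.** The study is a cohort with no comparison group named, so the time coefficient carries the effectiveness claim, which is one of two co-primary aims. A paired test compares each woman with herself. The model described compares time-point means within site, and those means need not come from the same women when a third give no follow-up. Stage of change is recorded through interaction with a system that women use at their own pace, so returning plausibly depends on continued engagement, and engagement may be related to the starting stage. If so, a change in who is measured would appear as a change in behaviour.

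**Working it through.** **1. Reproduce the plan's figures.** Inputs from the sample size section: difference 0.073, error term 0.287, two-sided alpha 0.05, power 0.80, design effect 1.3, and 2/3 providing data.

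- Paired formula: n = (SD × (z₀.₉₇₅ + z₀.₈₀) / difference)² = (0.287 × 2.802 / 0.073)² = 121.3, so 122. With the t distribution it is 124. The stated 125 is reproduced within 3%, reading 0.287 as a standard deviation. Read as a variance, it would give 423.
- Clustering: with ICC 0.012, 1 + (25 − 1) × 0.012 = 1.288 at 25 women per site, and 125 × 1.288 = 161, close to the stated 160.
- Loss: 160 / (2/3) = 240, or 20 per site.

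The 125, 160 and 240 therefore follow from a within-woman contrast among women with outcome data.

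**2. What the stated model estimates if all records enter.** Let r = 2/3 be the share who return, and let μR and μN be the baseline action/maintenance rates in returners and non-returners. Suppose no woman changes.

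- Baseline mean, all enrolled: r·μR + (1 − r)·μN
- 5.5-month mean, returners only: μR
- Apparent change: (1 − r)(μR − μN) = one third of the baseline gap

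The documents do not give the gap. Over an assumed range:

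| Assumed gap (points) | Apparent change (points) | Share of planned 7.3 |
|---|---|---|
| 5 | 1.7 | 23% |
| 10 | 3.3 | 46% |
| 15 | 5.0 | 68% |
| 20 | 6.7 | 91% |

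A gap of 3 × 7.3 = 21.9 points would produce the whole planned effect with no behaviour change. If returners start lower than non-returners, the sign reverses and real change is hidden. The shift depends on the fraction lost and not on the number enrolled, so a larger sample does not reduce it.

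**3. Simulation with no true change.** The written model was fitted to 240 women in 12 sites with two thirds returning, 300 runs per setting, and standard errors clustered on woman. A mean rate of 0.30, 20 risks per woman and a between-woman SD of 0.2 are assumptions.

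| Assumed gap (points) | All baseline records: mean rate ratio | All baseline records: rejections at 0.05 | Returners only: mean rate ratio | Returners only: rejections |
|---|---|---|---|---|
| 0 | 1.00 | 5% | 1.00 | 3% |
| 10 | 1.11 | 68% | 1.00 | 4% |
| 20 | 1.22 | 99% | 1.00 | 4% |

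Under the assumed SD, gaps of 10 and 20 points are 0.5 and 1 standard deviation, so the rejection rates are illustrative.

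**4. The other population question.** A within-woman contrast removes the shift but describes only women who returned. If the change is 7.3 points in returners and nil in the rest, the mean over all enrolled is 7.3 × 2/3 = 4.9 points.

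**The case against.** The strongest reply is that the article never says non-returners' baseline records enter the model. The paired planning test points to complete pairs, and the data collection section tracks baseline and then follow-up stage for each woman. The set of 240 at baseline against 160 at 5.5 months is thus one possible reading, and the analysis set is something a condensed article may leave to a fuller document. This stands against any flat statement that the plan pools the two groups. It does not settle the matter, because the article does state a model and that model is not the one the sample size rests on. The same section spells out restrictions by baseline stage, and the article names a multi-level model for staff scores, but no comparable structure is given for women.

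A reader might also infer that the bias must favour the intervention. The documents do not support that. Motivated women may return more, but women already at action or maintenance may have less reason to return, and staff follow-up of flagged risks also affects contact.

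Nor does the problem reach every effectiveness estimate. Forward progression and the per-risk outcome are defined relative to baseline, so a woman without follow-up has no value to contribute.

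Finally, the 4.9 figure reflects a choice of population and is not an error in the plan. Carrying baseline forward is a contestable single imputation. It would also be nearly empty as a condition on claiming success: for 160 returners t = 0.073 / (0.287/√160) = 3.22, and adding 80 zeros gives mean 0.0487, SD 0.237 and t = 3.18.

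**Conclusion.** The point holds as a conditional one, for the action/maintenance rate, which is the outcome that sets the sample size. The stated model and the paired planning basis do not match, and with one third expected to be lost, the mismatch can matter. If all available records are fitted, the time effect is shifted by one third of the returner/non-returner baseline gap: 1.7 to 5.0 points for assumed gaps of 5 to 15, against 7.3 planned. The direction is unknown. If only complete pairs are used, the shift is zero and what remains is that the estimate covers returners only. This goes beyond missing detail because a within-woman contrast is a better method than the one written and agrees with the study's own sample size. It should be corrected before analysis.

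**What to change.** Reconcile the Sample size and power calculation section with the Quantitative analysis section:

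- Make the primary 0 to 5.5 month contrast within woman, either by a woman-level effect in the Poisson model or by matched pairs of the same women, and say which records enter.
- Report baseline action/maintenance rates separately for women with and without 5.5-month data.
- Report alongside, and not as a condition on the conclusion, a sensitivity estimate for all enrolled women that keeps non-returners at their baseline stage.

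The cost is slightly more analysis on data already on the server. The drawback is that the all-enrolled estimate will be smaller than the returners' estimate.

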#### Qualitative data collection and measures

The academic partner (i.e. research staff) will engage key stakeholders from each site in virtual interviews prior to launching Gabby. We anticipate that 5–10 participants per site including frontline, administrative, and leadership staff will ensure that diverse perspectives and roles are represented, and will provide sufficient data for saturation, [37] although the exact number will be determined by community partner champions to reflect the organizational structure and workforce of the site. We will develop a semi-structured interview guide based on the CFIR domains (intervention characteristics, inner setting, outer setting, process, characteristics of individuals), select constructs within the domains, [30] and by adapting existing questions from the editable CFIR Interview Guide Tool [38]. Interview questions will examine perceptions of facilitators and challenges to implementing Gabby in community sites, the extent to which Gabby is congruent with the culture of each site, and organizational readiness.

The CFIR framework will also be used to guide identification of determinants of implementation, to select appropriate implementation strategies that match determinants identified, and to understand where those strategies can be employed in the implementation process. Strategy domains such as the action, action target, and implementation outcome affected will be outlined. This will ensure that the process for implementation is tailored to each site, directly informed by staff feedback, involves the engagement of site staff with different roles, and re-examines perceived barriers and facilitators over time. Data from this phase will be used to refine implementation strategies and inform appropriateness and acceptability implementation outcomes.

At the end of the implementation period leaders, clinicians, and administrative staff from each site who participated in the pre-launch phase will be invited to participate in an organizational stakeholder post-implementation virtual interview (Additional file 6). In the event of staff turnover, site champions will identify additional staff members to participate in a post-implementation interview. These data inform the feasibility implementation outcome, including staff perceptions of Gabby, the process of implementing the Gabby System within the community partner’s existing workflow and clinical context, and staff recommendations for scalability.

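### The sample size allows for within-site clustering, but the effectiveness test carries only site intercepts, so neither site differences in change nor repeated measures on each woman enter its standard error

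*Protocol article*

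**What the plan says.** Under Sample size and power calculation, the protocol article sizes a paired comparison of each woman's rate of risks at action or maintenance: "With paired two-sided tests, at a power of 0.80 and a significance level of 0.05, we would require at least 125 subjects". The inputs are an "approximately 7.3% difference in the rate of risks behaviors achieving action or maintenance from 0 to 5.5 months" and a figure of 28.7%, which the text labels a common error variance.

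It then gives the reason for inflating that number: "Because end-users are nested within sites, we also must account for within-site clustering". From "published intra-class correlation coefficient (ICC) data from 61 clinical practices in 8 practice based research networks on risks such as smoking, diet, and exercise", it states: "we anticipate an ICC of 0.012 and a design effect of 1.3". This takes 125 to 160 (13 per site at 12 sites). Allowing for one third without outcome data takes it to 240 (20 per site).

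Under Quantitative analysis, stage of change is measured at baseline, 3 months and 5.5 months. Effectiveness is tested "by using a Poisson model to regress our stage of change rate outcomes on data collection time point, with site fixed effects", at the 0.05 level. No site-by-time term, random effect, cluster-robust variance or term for the woman is named for this test. A multilevel random-effects model is named in the same section, but only for staff readiness scores.

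**The concern.** The sample size section treats clustering as part of the error of the change from 0 to 5.5 months. The analysis section gives that clustering no place in the test of the change.

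Every site contributes baseline and follow-up data, so the time contrast is made within sites and differences in site level cancel. What can still inflate the variance of the pooled change is variation between sites in the change itself, and a model with site intercepts alone sets that to zero. Some such variation is plausible here. Of the pre-launch work, the section on qualitative data collection says: "This will ensure that the process for implementation is tailored to each site, directly informed by staff feedback".

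A second gap lies in the same sentence of the analysis. The sample size assumes pairing within women, but the named model treats the measurements on one woman as independent once site and time are given.

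The two gaps push in opposite directions. Ignored variation in change makes the standard error too small. Ignored positive correlation within women makes it too large. Effectiveness is one of two co-primary aims, so a test whose actual level is unknown matters.

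**Working it through.** **Inputs** (Sample size and power calculation): change 7.3 points; 28.7 read as the SD of the change, because 125 is reproduced only on that reading although the text calls it a variance; two-sided 0.05; power 0.80; ICC 0.012; design effect 1.3; 12 sites; 13 per site.

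**1. The plan's own figures.**
- Paired n = ((1.960 + 0.842) × 28.7 / 7.3)² = 121.3, so 122 by the normal formula and 124 by noncentral t. The stated 125 is close.
- 125 × 1.3 = 162.5, stated as 160 (160/125 = 1.28).
- 160 / (2/3) = 240, or 20 per site.

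**2. Design effect against ICC.** Design effect = 1 + (m − 1) × ICC.
- m = 13: 1 + 12 × 0.012 = 1.144.
- Reaching 1.3 at ICC 0.012 needs m = 1 + 0.3/0.012 = 26.
- Reaching 1.3 at m = 13 needs ICC = 0.3/12 = 0.025.

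The stated 1.3, 0.012 and 13 do not fit together.

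**3. A paired test that ignores the design effect (DE).** Type I error = 2 × (1 − Φ(1.96/√DE)), taking DE as the variance inflation of the change.
- DE 1.3: 1.96/1.140 = 1.719, giving 8.6%.
- DE 1.144 (ICC 0.012, 13 per site): 1.96/1.070 = 1.832, giving 6.7%.
- DE 1.288 (ICC 0.012, 25 per site): 8.4%.

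Simulation with 12 sites of 13 and ICC of change 0.025 gave 8.1% to 8.8%.

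**4. The named structure, in a linear analogue.** Take two time points, site intercepts and no term for the woman, with within-woman correlation ρ. The model's variance for the time effect is about 2σ²/N. The true variance is 2σ²(1 − ρ) × DE/N. The ratio of true to model variance is DE × (1 − ρ). At DE 1.3:

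| ρ | Ratio | Error by formula | Error by simulation (12 × 13) |
|---|---|---|---|
| 0 | 1.30 | 8.6% | 8.9% |
| 0.3 | 0.91 | 4.0% | 4.3% |
| 0.5 | 0.65 | 1.5% | 1.8% |
| 0.7 | 0.39 | 0.2% | 0.2% |

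**5. The Poisson form itself.** This was simulated on assumed data: 12 sites of 13, 5 or 20 risks per woman, rate 0.2 or 0.4, woman SD 1 and site-slope SD 0 to 0.4 on the logit scale. The error ran from 0.5% to 24%. The article gives none of these inputs, so this is a range and not an estimate.

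**6. Inference on site as the cluster.** A t-test on the 12 site mean changes (11 degrees of freedom) simulated at 4.5% to 5.4% in every setting of ICC and ρ tried. Its power at 160 analysed comes from the noncentral t with noncentrality 7.3 / (28.7 × √(DE/160)):
- DE 1.3: noncentrality 2.82, power 0.73.
- DE 1.144: noncentrality 3.01, power 0.78.

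The plan's 0.80 is recovered at DE 1.3 only if the degrees of freedom are counted in women (159) and not in sites (11).

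**The case against.** A reader might infer that the effectiveness test runs at about 8.6%, with p-values too small and intervals too narrow. The document does not support that. The 8.6% belongs to a paired test, and the named model is not one. With moderate within-woman correlation the same structure is conservative, so even the direction of the error is open.

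The ICC is described only as being on risks. If it measures clustering of level, site intercepts absorb it, and the article contains no figure for clustering of change. That stands. It limits the error rates above to conditional statements, and it also removes the basis for the inflation to 160.

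Inference could be meant for these 12 sites only, and then variation in change between sites is not error. That is a legitimate reading of fixed effects, but it does not fit a sample size that inflates for clustering, and it leaves the repeated measures on each woman untouched.

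The section on study status says the analysis will take account of the periods before and after COVID-19 and of changes across and within organisations. It names no variance method. An unseen analysis plan might specify robust standard errors, but the article itself states the model and its handling of site, so the mismatch lies in what is written.

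It is also tempting to say that enrolling 25 per site, the lower end of the range in the abstract, restores power: 25 × 12 × 2/3 = 200 analysed, and about 0.82 on 11 degrees of freedom. That holds the design effect at 1.3 while site size rises to 16.7. With ICC 0.025 the design effect becomes 1 + 15.7 × 0.025 = 1.39 and power is 0.79. It is not a safe figure to write into the protocol.

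**Conclusion.** The concern holds in a limited form. The clustering allowance in the sample size has no counterpart in the named test, and the named test also drops the pairing that the sample size relies on. The actual level of the nominal 5% test cannot be determined from the article and may lie on either side of 5%.

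The figures of 8.6% and 6.7% are what a paired test would show if it ignored a design effect of 1.3 or 1.144. They assume that the design effect applies to change and that the sites stand for a wider set. On the same assumptions, power at 160 with site-level inference is about 0.73 to 0.78, not 0.80. This should be corrected. It does not undermine the design.

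**What to change.** In Quantitative analysis, base inference for the time effect on site as the cluster: site-clustered standard errors with a small-sample correction and t on 11 degrees of freedom. Because women are nested in sites, this covers both site variation in change and repeated measures within women. An alternative is a random site-by-time effect together with a random effect for the woman and allowance for overdispersion. A random site-by-time effect alone would still treat each woman's measurements as independent. Report the change for each site beside the pooled value, so that readers can see whether one or two sites drive it.

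In Sample size and power calculation, state that the design effect is assumed to apply to change, since the cited ICC is described only as being on risks. Reconcile 1.3 with ICC 0.012 at 13 per site (about 1.14). Restate power at 160 analysed on 11 degrees of freedom as about 0.73 (design effect 1.3) to 0.78 (ICC 0.012).

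The cost is analysis wording and a few lines of R. Intervals may widen, and the stated power becomes slightly less favourable.
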